### Inclusion and exclusion criteria

People enrolled into the study must be older than 80 years old and had to answer to the FGE questionnaire. People living in an institution (nursing homes or similar) have been excluded. Advanced mental impairment was not an exclusion criteria, but in such cases the consent have been signed by the closest relative who also answered to the questionnaire on behalf of the participant; this modality is foreseen by the extensors of the questionnaire, just for these cases. The selected patients have been contacted by phone and they underwent a face-to-face interview by trained personnel in the GP’s outpatient facility or at home if they were unable to go out.

### Sample size

The primary outcome is the difference in hospitalization and mortality rate between the LLE sample and the controls. Based on previous analyses, the three years expected hospital admission rate and death rate for the over-80 population accessing the standard of care are 35% and 25%, respectively. The maximum foreseen incidence rates in the population undergoing the LLE program intervention are 25% and 18% for hospitalization and death, respectively. The needed sample size in this case is 540 subjects per arm (Alpha error = 5%, Beta error = 20%). Based on the number of over-80s residents in Rome and Naples, a total sample of 1080 individuals is enough to assess differences in incidence rate per person/year higher than ±3%; a sample size of 600 individuals per each city is enough to assess differences in incidence rate higher than ±4%.

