### Outcomes

The following outcomes will be assessed for each site and each group :

Incidence of hospitalization and ER accessIncidence of deathIncidence of admission to LTC facilitiesLost to Follow Up (LTFU)

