## Figures and Tables

**Fig 1 f1-tmj-23-04-022:**
[figure not shown]
Level of frailty *“Long Live the Elderly!” program

**Table 1 t1-tmj-23-04-022:** the sample in the two cities involved

		LLE	Controls	Total
**Cities**	**Napoli**	250	203	453
	**Roma**	328	404	732
**Total**		578	607	1185

**Table 2 t2-tmj-23-04-022:** Baseline characteristics

		LLE * (%)	Controls (%)	Pearson Chi^2^
**Town**	**Rome**	44.8	55.2	0.01
	**Napoli**	55.2	44.8	
**Gender**	**Females**	68.7	58.5	<0.001
	**Males**	30.3	41.5	
**Age groups**	**<85**	56.8	69.0	<0.001
	**>85**	43.2	31.0	
**Education**	**Primary School**	78.2	67.2	<0.001
	**Secondary School/Degree**	21.8	32.8	
**Living arrangements**	**Alone**	15.9	18.3	0.536
	**Spouse**	59.7	58.6	
	**Other**	24.4	23.1	
**Comorbidity (more than one disease)**		87.3	92.7	<0.001

**Table 3 t3-tmj-23-04-022:** Mean Score per domain

	LLE	Controls	U Mann-Withney Test
			p
**Physical Area score**	−13.7 (SD ±13.8)	−10.5 (SD ±12.4)	<0.001
**Cognitive Area score**	−7.9 (SD±14.0)	−6.8 (SD±12.8)	NS
**Functional Area score**	28.6 (SD ±14.5)	29.5 (SD ±14.8)	NS
**Social Area score**	27.4 (SD ±5.9)	22.0 (SD ±6.1)	<0.001
**Economic Area score**	8.6 (SD±4.8)	9.8 (SD±5.5)	<0.001

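### The ±3% and ±4% precision figures are undefined, do not cover hospitalization at the design's 80% power, and the per-city figure is not delivered in Naples (453 enrolled, not 600)

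*Protocol article*

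**What the plan says.** The Sample size section of the protocol article names the between-group difference in hospitalization and mortality as the primary outcome. Its three-year control risks for hospital admission and death are given as "death rate for the over-80 population accessing the standard of care are 35% and 25%, respectively"; the risks for those "undergoing the LLE program intervention are 25% and 18% for hospitalization and death, respectively". It concludes: "The needed sample size in this case is 540 subjects per arm (Alpha error = 5%, Beta error = 20" per cent.

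Two precision statements follow, introduced by "Based on the number of over-80s residents in Rome and Naples". The first is that "a total sample of 1080 individuals is enough to assess differences in incidence rate per person/year higher than ±3" per cent. The second is that "a sample size of 600 individuals per each city is enough to assess differences in incidence rate higher than ±4" per cent. No formula is given, and the person-year unit is not repeated in the second statement.

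The Outcomes section adds: "The following outcomes will be assessed for each site and each group". Table 1 gives the enrolment: Naples 250 LLE and 203 controls (453), Rome 328 and 404 (732), overall 578 and 607 (1185).

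**The concern.** The ± figures are the only support in the article for looking at each city separately, and they can be read in more than one way. A reader who knows that the design uses 80% power may take them as detectable differences for either primary outcome. A reader used to survey work may take them as margins of error. Which outcomes and cities they cover depends on the reading.

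Naples also fell 147 short of the number called sufficient (147/600 = 24.5%), and the article does not comment on this. If the sentence stands, a null result in Naples could be taken as evidence that the programme has no effect there. For mortality, such a result is more likely than not even if the planned effect is real.

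**Working it through.** **Inputs.** Control and LLE three-year risks: death 25% and 18%, hospitalization 35% and 25%. Alpha 5%, power 80% (all from Sample size). Enrolment from Table 1. Assumptions: two-sided test (sidedness is not stated, but two-sided reproduces the plan's figure); 1:1 split of the 600 per city; constant rates, first events and full three-year follow-up wherever person-years are used.

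**1. The plan's own sample size.** Pooled-variance formula for two proportions, no continuity correction:

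n = [1.96·√(2p̄(1−p̄)) + 0.8416·√(p₁(1−p₁)+p₂(1−p₂))]² / (p₁−p₂)²

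- Death: [1.96·√0.33755 + 0.8416·√0.3351]² / 0.07² = 539.5, so 540 per arm. This matches exactly.
- Hospitalization: [1.96·√0.42 + 0.8416·√0.415]² / 0.10² = 328.5, so 329 per arm. Death sets the size.

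**2. Single-proportion margin at 50%.** 1.96·0.5/√1080 = 2.98% and 1.96·0.5/√600 = 4.00%. Both stated figures match.

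**3. Detectable difference at 80% power.** Hold the control risk fixed, solve the power formula for the LLE risk, then convert both to yearly rates by −ln(1−p)/3. For death at 540 per arm: 25% gives 9.59 and 18.0% gives 6.62 per 100 person-years, a difference of 2.97.

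| Control / LLE | Death: LLE risk | Risk difference (points) | Per 100 person-years | Hosp.: LLE risk | Risk difference (points) | Per 100 person-years |
|---|---|---|---|---|---|---|
| 540 / 540 | 18.0% | 7.0 | 2.97 | 27.1% | 7.9 | 3.8 |
| 300 / 300 | 15.8% | 9.2 | 3.9 | 24.6% | 10.4 | 5.0 |
| Naples 203 / 250 | 14.5% | 10.5 | 4.4 | 23.1% | 12.0 | 5.6 |
| Rome 404 / 328 | 16.5% | 8.5 | 3.6 | 25.4% | 9.6 | 4.6 |
| Overall 607 / 578 | 18.3% | 6.7 | 2.8 | 27.5% | 7.5 | 3.7 |

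On this reading ±3% and ±4% hold at the planned sizes for death and fail for hospitalization. A formula applied directly to the rates gives slightly different values (Naples 4.7 and 5.9) and the same pattern.

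**4. 95% half-width of the person-year rate difference.** 1.96·√(λ₁²/d₁ + λ₂²/d₂), where λ is the yearly rate and d = n·p is the expected number of events. For death at 540 per arm: 1.96·√(0.0959²/135 + 0.0662²/97.2) = 2.1 per 100 person-years.

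| Sizes | Death | Hospitalization |
|---|---|---|
| 540 per arm | 2.1 | 2.6 |
| 300 per arm | 2.8 | 3.5 |
| Naples as enrolled | 3.3 | 4.1 |

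On this reading both figures hold at the planned sizes. In Naples hospitalization just misses ±4%. With only one year of follow-up the half-widths are 3.4 and 4.1 (540 per arm) and 4.6 and 5.5 (300 per arm), which exceed the stated figures.

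**5. Power for the planned effects.** Power = Φ{[|p₁−p₂| − 1.96·√(p̄(1−p̄)(1/n₁+1/n₂))] / √(p₁(1−p₁)/n₁ + p₂(1−p₂)/n₂)}. For death in Naples, p̄ = (203·0.25 + 250·0.18)/453 = 0.2114, and (0.0700 − 0.0756)/0.0389 = −0.14, giving 44%.

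| Sizes | Death | Hospitalization |
|---|---|---|
| 300 per arm | 55% | 76% |
| Naples | 44% | 64% |
| Rome | 63% | 84% |
| Overall 578 / 607 | 83% | 96% |

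The planned death effect is 2.97 per 100 person-years, below 4. So even a city that reached 600 was not sized to detect it at 80% power.

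**The case against.** The strongest reply is that the sentence can be true as worded. It speaks of differences per person-year. On that scale 1080 people detect a death difference of 2.97 at 80% power and 600 detect 3.9, while the 95% half-widths for both outcomes lie inside ±3 and ±4. This stands. The match with a single-proportion margin, and the appeal to the number of residents, might lead a reader to infer that a pooled survey margin was mistaken for a group difference. The text shows no formula, two explanations fit equally well, and so that inference is not established.

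A reader might also see a contradiction in 600 per city (1200 in all) against a total of 1080. These are two separate statements of sufficiency, and the article does not set 1200 as a target; Rome enrolled 732.

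It is also fair to say that the article specifies no hypothesis test by city, and that such detail usually sits in an analysis plan. But the article itself states a per-city precision and a per-site assessment, and its own Table 1 shows that the number behind that precision was not reached in Naples.

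**Conclusion.** The point holds in limited form and is moderate. The ± figures lack a definition, an outcome and, for the city figure, a time scale. At 80% power they cover death but not hospitalization (3.8 against 3, and 5.0 against 4, per 100 person-years). As 95% half-widths they cover both outcomes at the planned sizes, so it would be wrong to say that the study cannot deliver them on any reading.

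In Naples the ±4% is missed on every reading checked except the half-width for death, and power for the planned effects is low for death in particular.

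None of this touches the primary comparison: overall enrolment exceeds 540 per arm. The person-year results rest on constant rates, first events and complete three-year follow-up; losses would make them less favourable.

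**What to change.** Replace the ±3% and ±4% sentence with the between-group difference detectable at 80% power (two-sided 5%), by outcome and for the enrolled numbers. As three-year risk differences for death and hospitalization these are 6.7 and 7.5 points overall, 10.5 and 12.0 in Naples, and 8.5 and 9.6 in Rome. Name the scale, the control risks of 25% and 35%, and the follow-up assumption. If a half-width is what was meant, say so and give it separately for each outcome.

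State that 453 were enrolled in Naples, and that results by city are estimates with confidence intervals, so that a null finding there is not read as absence of effect.

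The cost is wording only. No sample size or analysis of the primary comparison changes; the stated precision becomes less favourable.

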### Baseline assessment

The FGE questionnaire provides a multidimensional assessment and allows a definition of frailty using a final score [14,17]. The FGE has been validated by the researchers of Biomedicine and Prevention Department of University of Rome “Tor Vergata” as predictor of death, hospital use and need of LTC, and used in several studies. It consists of four sections:

Demographic informationMultidimensional evaluation (physical, mental and functional status, socio-economic resources, environment): a score is given to each domain of this section and contributes to the Final Score. in each domain, as it is for the Final Score, the higher is the score the better the client’s situationA list of diseases affecting the patients, compiled by the GPsActivities of Daily Life (ADL) according to Katz and Instrumental Activities of Daily Life (IADL) according to Lawton.

The Multidimensional evaluation (section b) contributes to generate a Final Score, that ranges from −108 to 101 while the other information are used as independent variables. According to the Final Synthetic Score (FSS) the subjects are classified in 4 groups: Robust : FSS >70; Pre-frail: FSS 50–70; Frail: FSS 11–49; Very Frail: FSS <10

### Follow up data collection

Follow up data will be gathered every six months over a period of three years. Data will be collected through:

Phone interviews to enrolled subjectsPhone interviews to enrolled subjects’ GPsInformation gathered from Regional data base on:○ Hospital admissions and Emergency Room (ER) accesses○ Mortality○ Admissions to LTC facilities○ Use of home care services

### Outcomes

The following outcomes will be assessed for each site and each group :

Incidence of hospitalization and ER accessIncidence of deathIncidence of admission to LTC facilitiesLost to Follow Up (LTFU)

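### The claim that 600 people per city suffice to assess differences above ±4% does not match the enrolled numbers or the planned mortality effect; city results should be reported as estimates only

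*Protocol article*

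**What the plan says.** The Sample size section sets one contrast across both cities: "The primary outcome is the difference in hospitalization and mortality rate between the LLE sample and the controls". Under standard care it expects 35% to be hospitalised and 25% to die within three years. For the programme group it assumes at most 25% and 18%. It concludes: "The needed sample size in this case is 540 subjects per arm (Alpha error = 5%, Beta error = 20" per cent).

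The same section then makes two further adequacy statements. One is for the whole study: "a total sample of 1080 individuals is enough to assess differences in incidence rate per person/year higher than ±3" per cent. The other is for each city: "a sample size of 600 individuals per each city is enough to assess differences in incidence rate higher than ±4" per cent. The second does not say whether its ±4% is also per person-year.

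The Outcomes section opens its list of hospitalisation and emergency access, death, long-term care admission and loss to follow-up with "The following outcomes will be assessed for each site and each group".

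Table 1, captioned "the sample in the two cities involved", gives Naples 250 LLE and 203 controls (453), and Rome 328 LLE and 404 controls (732).

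**The concern.** The city-level sentence and the Outcomes sentence together present a comparison within each city as a planned use of the data that the sample size supports. The 540 per arm applies to both cities combined, so half of it, or less, cannot carry the same question in one city. A reader who relies on the 600-per-city sentence could take a non-significant result in Naples as evidence that the programme does not work there, when the Naples sample was more likely than not to miss the planned mortality effect.

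The groups are also unevenly spread over the two cities. If outcome rates differ between Rome and Naples, a crude pooled comparison would mix that difference into the programme effect.

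**Working it through.** **Inputs.** Death 25% versus 18%, hospitalisation 35% versus 25%, alpha 5%, power 80% (Sample size section); counts by city (Table 1). Assumed: two-sided test, no loss to follow-up, no clustering by general practitioner, unadjusted proportions.

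**1. The plan's own figure.** For death, with mean risk 0.215:

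n = [1.960·√(2·0.215·0.785) + 0.842·√(0.25·0.75 + 0.18·0.82)]² / 0.07² = (1.960·0.5810 + 0.842·0.5789)² / 0.0049 ≈ 539.5, so 540 per arm.

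This matches. A one-sided test would need 425, so 540 fits a two-sided 5% test. Hospitalisation alone would need 329; mortality drives the size.

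**2. Power for the planned effects.** Power = Φ[(Δ − 1.96·SE₀)/SE₁], where SE₀ uses the pooled risk and SE₁ the separate risks.

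| Sample (LLE vs controls) | Death: SE₀, SE₁ | Power, death | Power, hospitalisation |
|---|---|---|---|
| Pooled, 578 vs 607 | 0.0239, 0.0238 | 83.5% | 96.4% |
| Rome, 328 vs 404 | 0.0307, 0.0302 | 62.7% | 83.6% |
| Naples, 250 vs 203 | 0.0386, 0.0389 | 44.3% | 64.1% |
| A city of 600, 300 per arm | 0.0335, 0.0334 | 55.1% | 76.3% |

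Example, Naples, death: (0.07 − 1.96·0.0386)/0.0389 = −0.14, and Φ(−0.14) ≈ 44%.

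**3. What ±4% could mean for a city of 600.**

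- *Difference in three-year risk.* For 25% versus 21% with 300 per arm, SE₀ = √(0.23·0.77·2/300) = 0.0344 and SE₁ = 0.0343. Power = Φ[(0.04 − 0.0673)/0.0343] ≈ 21%.
- *Difference per person-year.* With a constant hazard, rate = −ln(1 − risk)/3: 0.0959 for controls, 0.0662 for LLE, a difference of 0.0297, about 3.0 points. (Simple division gives 7/3 = 2.3.) Both are below 4. For a true 4-point difference (0.0959 versus 0.0559, the latter a three-year risk of 15.4%), person-years are n·risk/rate. Naples: 203·0.25/0.0959 = 529 and 250·0.154/0.0559 ≈ 690; SE = √(0.0959/529 + 0.0559/690) = 0.0162; power = Φ(0.04/0.0162 − 1.96) ≈ 70%. The same steps give about 83% at 300 per arm and about 90% in Rome.
- *Precision of one proportion.* 1.96·√(0.25/600) = 4.00% and 1.96·√(0.25/1080) = 2.98%. Both published figures match the 95% half-width of a single proportion at 50%, which is not a between-group comparison.

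**4. Precision by city for the death difference** (1.96·SE₁): Naples ±7.6 points (1.96·0.0389), Rome ±5.9 (1.96·0.0302), pooled ±4.7 (1.96·0.0238), against a planned effect of 7.

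**5. A group-by-city test.** SE for death = √(0.0389² + 0.0302²) = 0.0493. The difference between cities detectable with 80% power is (1.960 + 0.842)·0.0493 = 13.8 points, about twice the whole planned effect. For hospitalisation it is 15.4 points, against a planned 10.

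**6. Balance over cities.** Rome supplies 328/578 = 57% of the LLE group and 404/607 = 67% of controls.

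**The case against.** The strongest reply is that the 600-per-city sentence can be read so that it is true. If ±4% is per person-year, like the ±3% before it, 300 per arm has about 83% power for a 4-point difference in deaths. The sentence is also conditional: it says what 600 would achieve, not that 600 were targeted. Rome, with 732, meets the condition and has 84% power for the planned hospitalisation difference. All of this stands. It does not help Naples, which has 453, and it does not help mortality in either city, because the planned effect is below 4 points per person-year.

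A second reply is that the Outcomes sentence may announce only tabulation. Its list includes loss to follow-up, and it names no test by city. This also stands, and it limits the point.

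A reader might go further and infer that the plan has no deciding pooled contrast and will produce conflicting city verdicts. If each city were judged by its own p-value under an equal true effect, exactly one would be significant for death with probability 0.627·0.557 + 0.443·0.373 ≈ 51% (41% for hospitalisation). If any of the pooled, Rome and Naples results counted as success, the error under no effect would be about 11.5% by simulation. The document does not support that inference. It names a pooled primary contrast with its own sample size, and it states neither of those decision rules. Even in the 51%, a split means significant against non-significant; estimates in opposite directions would occur only about 4.6% of the time for death. An interaction test or an exploratory label may sit in an analysis plan that is not shown, so their absence from the article is no finding.

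**Conclusion.** The point holds in a limited form. The pooled primary contrast is defined and correctly sized, and the enrolled sample gives it 83% power for death. What fails is the stated city-level adequacy. Naples is 147 short of the 600 named (600 − 453), power for the planned mortality difference is about 44% there and 63% in Rome, and even 300 per arm would give 55%. On the reading kindest to the plan, Naples has about 70% power for a difference larger than the one planned.

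These figures assume a two-sided 5% test, the plan's own event rates in both cities, a constant hazard for the person-year reading, no loss to follow-up and no clustering. Controls were drawn ten per general practitioner, so allowing for clustering or for loss would lower the city-level power further. The pooled contrast itself is not in doubt on this ground, but the uneven city mix is a reason to account for city in it.

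**What to change.** 1. In the Sample size section, remove the 600-per-city sentence or correct it: say whether ±4% is a three-year or a person-year figure, and whether it is precision or a detectable difference. State the power or precision for the enrolled numbers (for death, about 44% and ±7.6 points in Naples, 63% and ±5.9 points in Rome).
2. State that each primary outcome is decided by the pooled LLE-versus-control contrast, stratified by or adjusted for city. Power is essentially unchanged (83.4% stratified against 83.5%). The Abstract's list of adjustment variables does not name city.
3. In the Outcomes section, say that city results are reported as estimates with 95% confidence intervals, and that no claim of effect or lack of effect rests on one city.
4. If a group-by-city test is run, label it as low-powered: 80% power only for a between-city difference in effect of about 14 points for death.

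The cost is a few sentences and one stratification factor, using data already collected. The downside is that the sponsor gives up stand-alone claims for each city.

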### Statistical Methods

Continuous and categorical variables have been displayed; differences between the two groups have been tested by parametric and non parametric tests. The statistical analysis was performed through IBM SPSS Statistics 25.0,

## III. RESULTS

The sample was made up by 1,185 individuals, 578 included in the LLE program and 607 controls (Table 1).

Mean age was quite similar between the two groups (84.8±5.7 and 83.7±4.8 for LLE and controls, respectively) even if the difference is statistically significant (U-Mann-Withney Test; p<0.001). However, Table 2 shows baseline characteristics and some significant statistic differences: female gender is less represented among the controls as well as the older age group (people> 85 years old are 43.2% vs 31.0% among cases and controls respectively). Controls are also more educated while living arrangements do not show statistic significant differences. Comorbidity is more prevalent among the controls (92.7% vs 87.3%) even if the median of the number of pathologies is 4 for the controls and 5 for LLE group (p = 0.025).

The assessment of frailty shows that the control group is less likely to be frail than the LLE group: overall frail and very frail individuals are less than 40% in the control group while the percentage is close to 50% among the LLE group (Chi-square test; p=0.005) (Fig 1).

With regard to the single domain of the assessment of frailty (Table 3), the control group shows a better Physical Area Score (−10.5 vs −13.7, p<0.001) and a better Economic Area score (9.8 vs 8.6, p<0.001). However, the LLE group shows a better score in the Social Area (27.4 vs 22.0, p<0.001).

Interestingly, comorbidity was correlated to each Area score with statistic significance (Pearson correlation: p<0.01 for each score) as well as with FGE Final Score, but it did not correlate with age.

## IV. DISCUSSION

The paper reports on the design of a longitudinal pragmatic trial aimed at evaluating the impact of a community care intervention based on the assessment of frailty and on counteracting social isolation in two Italian cities with a low rate of community care services. The sample is made up by two population of over-80s individuals: the first one accessing the standard of care and the second one included in the LLE program. The differences between the two samples are due to the trial design aimed at comparing populations who underwent different care interventions. In this case, the differences reported by the paper in physical or social areas score are crucial to assess any gap among the outcomes. Bio-psycho-social frailty is associated to an increase of mortality and use of hospital services; social isolation is considered a major risk factor for developing frailty[18–20] as well as specific diseases associated to advanced frailty (like dementia) [21], especially in the older adult population. It is likely that a program focused on counteracting social isolation is able to slow down or even reverse the progression towards frailty and reduce the incidence of negative events [12, 14, 22]. Some evidence is already documented; however, to our knowledge, it is the first time that such a program is tested in a pragmatic trial at community level.

The effectiveness of intervention aimed to counteract loneliness or social isolation has been discussed since many years ago [23]. The questions raised are often methodological, but there is also another issue: most of the studied interventions are addressing strictly social problems, without considering the inextricable intertwining between social and health issues. In many cases, group interventions have been considered more effective than interventions targeting the individual in his/her own living environment. However, even in this case the impact on the citizens’ health and on their use of health care services were not assessed [24].

Fairhall and coll. performed a randomized clinical trial on a sample of individuals assessed for physical frailty according to the Fried criteria: they tested an intervention aimed at improving physical performance of part of the sample to be compared with the other ones who accessed the standard of care. They pointed out the positive impact of the intervention, especially for males, and for “very frail” subjects i.e. participants who met >3 Cardiovascular Health Study frailty criteria. In this case, the assessed intervention was trying to improve the patients’ health status, starting from an assessment of patients’ functional health [25,26].

In our case, we are going to test a different intervention based on the provision of social and health integrated care: frail participants will be supported through an ICP drafted by the social worker and the community nurse (when available) or by other professionals like the GP according to the needs of the client and the availability of other professionals to be involved in the program. The assessment of strong outcome indicators like mortality and use of hospital and non-hospital care services strengthens the analysis from a public health point of view [27], and it is in line with the hypothesis to be tested: social intervention are able to improve health and quality of life of participants. The program acts as a case manager, able to involve formal and informal care givers, like relatives or neighbours, whose availability has been previously asked on a voluntary basis or who are operating on the field (as the home care services by municipality or by regional health system).

The two groups show some differences as it occurs in a real world setting: in fact the two samples stems from the Community-based pro-Active Monitoring Program “Long Live the Elderly!” that is an ordinary service ongoing since 2004,, compared with an a cohort set up for this comparison. The main differences are about the physical condition area score, that is worse in the LLE group which at the same time shows higher social resources: this could be understandable since the LLE program is aimed at increasing the social capital at both individual and community level. We are probably witnessing one of the impacts of the program. It is also likely that individuals with advanced physical impairment can stay at home in case of the presence of a supportive social environment able to provide a certain amount of simple daily care. This is even more interesting because the LLE group shows a lower education level which is a proxy of the individual social and economic background with no great differences in the living arrangements. Cognitive and Functional area score have no significant differences between the two groups. It appears that the condition strictly associated to social background of the individuals are worse in the LLE group, so that the better score in the Social Area is due to other factors related to social relationships or to the intervention of formal care services catalyzed by the program.

